**Fig. 2 Fig2:**
[figure not shown]
Diagram of wearable device usage. **A**, **B** The numbers and arrows are positioned on the front of the leg or foot and centered, as shown in the figure. **C**, **D** Straight leg raised to the green area is considered effective

### Outcome measures

At the time of hospitalization, all recruited patients complete baseline registration which includes gender, age, BMI (kg/m^2^), education level, medical insurance, dwelling place, comorbidities, and medications. Clinical assessments such as knee extension and flexion, KSS, WOMAC, and the American Society of Anesthesiologists (ASA) physical status classification are also completed. At 2 weeks, 12 weeks, and 24 weeks after discharge, 6WMT, ROM, VAS, KSS, and WOMAC of patients are evaluated. The cost and time are calculated at 12 weeks after discharge.

### Primary outcome

The primary outcome measures of this study are the cost and time spent on medical care within 12 weeks after discharge. This includes costs for transportation, consultations, mobility aids, imaging examinations, and medications, as well as the time spent during the medical visit. All costs and time are recorded in a diary. Each entry in the diary must include the date, expenses, and time spent, along with the reasons. The diary is provided to the patients in both groups by the physiotherapists before discharge for free. The unit of cost is RMB, and the unit of time is hours.

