**Method/design:**

This is a single-center, single-blinded, parallel randomized controlled trial conducted at Xi'an Honghui Hospital, a regional orthopedic medical center. Eligible patients will be recruited to participate in the study, and baseline data collection and clinical assessments will be conducted at the time of admission. Using the principle of random allocation, recruited patients will be divided into either the experimental or control group. Both groups will undergo a standard, widely promoted rehabilitation program. The patients in the experimental group will wear equipment to detect and track mobility in the lower limbs. All patients will return to the outpatient clinic for follow-up assessments at 2 weeks, 12 weeks, and 24 weeks after discharge, where outcome indicators will be measured. The primary outcome will be the cost and time after discharge, while secondary outcomes will include the 6-min walk test (6MWT), range of motion (ROM), visual analog scale (VAS), American Knee Society Score (KSS), the Western Ontario and McMaster Universities Osteoarthritis Index (WOMAC).

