**Discussion:**

We should encourage the adoption of novel, easy-to-use, supervised devices if they prove to be beneficial for patients in terms of cost, time, and effectiveness after TKA. This type of device is particularly important for people in remote rural areas, those with limited financial resources, and those who are reluctant to return to hospitals for follow-up care.

*Trial registration* Chinese Clinical Trial Registry ChiCTR2300068418. Registered on 17 February 2023.

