### Interventions

During their hospitalization, both the experimental and control groups receive the same treatment regimen, rehabilitation exercise, and nursing services. After undergoing TKA, patients in the experimental group are given wearable devices and are guided to perform rehabilitation training using an APP, while patients in the control group follow a handbook for their exercise program. The rehabilitation programs for both groups are consistent and were developed in accordance with the American Academy of Orthopaedic Surgeons (AAOS) Clinical Practice Guidelines (CGPs), the American Association of Hip and Knee Surgeons (AAHKS) guidelines, and other published literature [9, 32–34]. The rehabilitation exercise program can be found in Additional file 2. Following their discharge, both groups perform the home-based exercise program for 12 weeks. The patients in the experimental group will be required to return the devices to the research team at the 12th week. Following that, both groups of patients will no longer be required to adhere to the rehabilitation program's exercise regimen.

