### Experimental group and equipment components

The patients will require assistance from the doctors to download the APP and connect the devices. The devices consist of two small monitors, which are placed about 5 cm above and below the knee joint when exercising the knee joint, and about 5 cm below the knee and the dorsum of the foot when exercising the ankle joint (refer to Fig. 2). These devices can monitor the magnitude and completion of exercises and then upload the data to the physicians' workstation. Patients can watch instructional videos on the APP to learn how to wear and exercise with the devices and then start exercising actively. The APP provides prompts for exercise frequency and whether the exercise target is reached by voice. Patients can view their exercise progress on the APP, such as the completion rate and compliance rate. Additionally, they can upload their own functional and symptomatic information to the APP, such as lower limb swelling, ecchymosis, and wound healing, in the form of videos or pictures.

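### The diary-based primary cost outcome captures patient-borne spending only, so it cannot by itself show that the wearable-device approach saves cost overall

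*Protocol article*

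**What the plan says.** **Outcome and source.** The Primary outcome section states: "The primary outcome measures of this study are the cost and time spent on medical care within 12 weeks after discharge". It then describes the content: "This includes costs for transportation, consultations, mobility aids, imaging examinations, and medications, as well as the time spent during the medical visit". On the source it says: "All costs and time are recorded in a diary". The physiotherapists hand the diary to patients in both arms before discharge. No hospital, sponsor or insurer cost record is mentioned, and no section states whose costs are meant.

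**Resources used in one arm only.** Under Interventions, "patients in the experimental group are given wearable devices and are guided to perform rehabilitation training using an APP", while controls follow a handbook. The device is a loan: "The patients in the experimental group will be required to return the devices to the research team at the 12th week". Under Experimental group and equipment components, staff input is added: "The patients will require assistance from the doctors to download the APP and connect the devices". The same section says that exercise data go to the physicians' workstation.

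**What the result is for.** The Background motivates the trial by the strain on health budgets and the cost of care, and sets the aim of evaluating cost, time savings and effectiveness of the new approach. The Discussion paragraph of the abstract encourages "adoption of novel, easy-to-use, supervised devices if they prove to be beneficial for patients in terms of cost", together with time and effectiveness.

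**The concern.** The approach under test consumes resources that the comparator does not: a device, an app, doctors' time for set-up and possibly clinician time to follow the uploaded data. A patient can record only what the patient pays. For the experimental arm these resources enter the outcome as zero unless they are charged to the patient.

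The omission is one-sided. It can only favour the experimental arm, and neither randomisation nor a larger sample removes it. If the diary cost is lower and the report says that the approach saves cost, a reader deciding on adoption would take this as a net saving. Outside the trial somebody has to pay for the device and the monitoring, whether patient, hospital or insurer, and the protocol article does not say who.

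**Working it through.** **Inputs from the Sample size section:** planned difference 2000 RMB, SD 3987 RMB, two-sided alpha 0.05, power 0.90, stated n = 80 per group.

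**1. The plan's own figure.** n = 2(z_alpha + z_beta)² × SD² / difference² = 2 × (1.960 + 1.282)² × 3987² / 2000² = 83.5, so 84 per group against the stated 80. Power at 80 per group is 0.887. The shortfall is small and is a separate matter. What counts here is that the planned effect is 2000 RMB.

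**2. Which resources reach the outcome.**

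| Resource | Arm | Named as a cost item? | Can a patient diary record it? |
|---|---|---|---|
| Transport, consultations, mobility aids, imaging, medication | Both | Yes | Yes |
| Device on loan | Experimental | No | Only if charged to the patient |
| App | Experimental | No | Only if charged to the patient |
| Doctors' set-up time | Experimental | No | Only if charged to the patient |
| Monitoring at the workstation | Experimental | No | Only if charged to the patient |

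**3. Effect on the saving.** Let S be the diary saving (mean control minus mean experimental) and c the uncounted intervention cost per experimental patient. Net saving = S − c. The documents give no value for c, so the values below are assumptions. They also assume that the planned 2000 RMB does not already allow for intervention cost; the Sample size section does not say.

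| Assumed c (RMB) | Net saving if S = 2000 (RMB) |
|---|---|
| 500 | 1500 |
| 1000 | 1000 |
| 1500 | 500 |
| 2000 | 0 |

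Above 2000 RMB the sign reverses. In general, the break-even intervention cost equals the diary saving itself.

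**4. How small a significant diary saving could be.** With 80 per group, SE = 3987 × √(2/80) = 630.4 RMB. The smallest observed difference with p < 0.05 is 1.960 × 630.4 ≈ 1236 RMB. At the Bonferroni threshold of 0.002 in Data analysis it is about 1948 RMB. An uncounted cost of that size would cancel a saving that had just reached significance.

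**5. Scheduled follow-up visits.** The abstract says: "All patients will return to the outpatient clinic for follow-up assessments at 2 weeks, 12 weeks, and 24 weeks after discharge". If each arm carries the same expected visit cost v, it drops out: (control + v) − (experimental + v) = control − experimental, a change of 0 RMB. Only the variance can grow. With an assumed independent visit-cost SD of 500 or 1000 RMB, the total SD is √(3987² + 500²) = 4018 or √(3987² + 1000²) = 4110, and n per group moves from 84 to 85 or 89.

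**The case against.** **The patient's perspective is legitimate.** The adoption statement speaks of benefit for patients, and the abstract stresses people with limited means. Spending and hours from a patient diary suit that question. This stands: the outcome is valid for patient-borne cost. A reader might infer that the primary outcome is invalid or that no cost claim is possible, and the documents do not support that. However, the Background also argues from health budgets and the cost of care, and no perspective is declared that would confine the claim to patients.

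**The item list is open.** It is introduced as a list of inclusions, and the diary takes in all costs, so a charge to the patient for device or app would be caught. This also stands, and the article does not say outright that the device is free of charge. It does not help with resources that the patient never pays for, since the diary is the only source stated.

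**The article is condensed.** Unit costs may well sit in a fuller document, and their absence is not the point. The content and source of the primary outcome are fixed here, and they do not match the breadth of the aim stated here.

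**The size is unknown.** This is correct. A returned device can be re-used, so c per patient may be small. It would also be tempting to compute a loss of power for net cost, but the planned test is on diary cost, so such figures would not describe this trial.

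**Conclusion.** The point holds in a limited form. As written, the primary outcome measures what patients spend. It can support a statement that patients in the experimental arm paid less within 12 weeks of discharge. It cannot support a statement that the approach saves cost overall, because the resources of the intervention itself fall in one arm and are uncounted unless charged to the patient.

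The size depends entirely on c, which the documents do not give. The 500 to 1500 RMB range is an illustration, and it takes the planned 2000 RMB as a diary saving.

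A reader might also infer that the follow-up visits at 2 and 12 weeks make a saving an artefact. The documents do not support this. They do not say whether these visits are counted, and the visits are scheduled alike in both arms. At most they add noise.

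**What to change.** 1. State the cost perspective, and label the diary outcome as patient-borne cost. It can remain the primary outcome.
2. Pre-specify a supplementary net-cost analysis: net cost = diary cost + c for each experimental patient. Here c is a fixed sum of the device cost amortised over re-use, the app, set-up time and monitoring time at stated unit costs. Anything already charged to the patient and entered in the diary must not be added twice. Report the difference in mean net cost with a confidence interval.
3. Give a sensitivity range for c, covering re-use count and staff time, and report the break-even value at which the saving disappears.
4. Tie any general cost-saving or adoption claim to net cost. Otherwise confine the claim to patient-borne cost.

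The change needs no additional patients, visits or diary fields. It costs some work to obtain unit costs and one more analysis. The downside for the sponsor is a smaller apparent saving.

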Wearable micro-sensing devices have become commonplace in the sports industry for real-time performance analysis of athletes [23, 24]. For instance, in the case of total hip arthroplasty and cardiovascular risk factors, accelerometry can be employed to monitor physical activity levels and estimate calories and energy expenditure by tracking movement patterns, including steps taken and distance traveled [25–27]. However, their potential use in healthcare has yet to be fully realized [28]. The number of studies on wearable motion sensors has grown in recent years, with many focused on knee replacements, providing additional information to clinical metrics [29]. This study aims to evaluate the cost, time savings and effectiveness of an innovative treatment approach using a new, simple monitoring device in conjunction with a mobile phone app to guide patient rehabilitation exercise. We hypothesize that patients in the experimental group would exhibit improved short-term functional outcomes and experience cost and time savings compared to patients in the control group.

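### The co-primary time outcome names only time during medical visits and does not say whether app and device care, given to one arm only, is counted

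*Protocol article*

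**What the plan says.** The Primary outcome section states: "The primary outcome measures of this study are the cost and time spent on medical care within 12 weeks after discharge". It then itemises five kinds of cost (transport, consultations, mobility aids, imaging, medication) and one kind of time: "as well as the time spent during the medical visit". Both are kept in a patient diary, with this rule: "Each entry in the diary must include the date, expenses, and time spent, along with the reasons". The same diary goes to both arms: "The diary is provided to the patients in both groups by the physiotherapists before discharge for free".

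The arms differ in what patients do at home. Under Interventions, "patients in the control group follow a handbook for their exercise program". Under Experimental group and equipment components, "The devices consist of two small monitors, which are placed about 5 cm above and below the knee joint when exercising the knee joint", with another placement for ankle exercises. The app carries videos on wearing the devices and exercising with them, exercise data go to the physicians' workstation, and patients may send in clinical information: "they can upload their own functional and symptomatic information to the APP, such as lower limb swelling, ecchymosis, and wound healing".

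The Background hypothesis is that experimental patients will "experience cost and time savings compared to patients in the control group". The Sample size section confirms that cost and time are the two primary outcomes.

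**The concern.** The outcome has a broad name, while its one stated time component is narrow. What falls between the two is care delivered remotely, and the intervention consists largely of that. The exercise programme is meant to be the same in both arms, so exercise time should largely cancel. Handling the devices and sending material to the team does not cancel, because control patients have no sensors and no app.

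The design makes this gap matter. Both arms attend the scheduled follow-ups at 2 and 12 weeks, so a difference in visit time must come mainly from other visits. The article's Discussion presents the device as a way round distance and transport barriers, so replacing clinic contact with remote contact is part of its rationale. If an avoided visit is counted in full and the contact that replaced it is not counted, the trial could report a time saving on a primary outcome when only clinic time had fallen. The abstract ties encouraging adoption of such devices to benefit in cost, time and effectiveness.

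**Working it through.** **No figure to reproduce.** The Sample size section shows its calculation for cost only. It gives no effect size, standard deviation or sample size for time. Nor do the documents give a duration for a visit, a journey, a sensor fitting or an upload. The check is therefore a comparison of the two readings, followed by an illustration under stated assumptions.

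**Reading A: only visit time counts.** Per experimental patient, relative to control, let K be the number of visits avoided, v the hours per visit, t the travel hours per visit, and r the extra hours of remote care.

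- Saving recorded by the outcome: K × v
- Saving in all patient time on care: K × (v + t) − r
- Recorded minus actual: K × v − [K × (v + t) − r] = r − K × t

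The recorded saving is too large if r exceeds K × t, and too small if K × t exceeds r. Taken alone, the remote-care omission pushes towards the hypothesis. Leaving out travel pushes the other way. The documents give neither r, K nor t, so the sign of the net error is open.

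**Reading B: all time on medical care counts.** A diary entry needs a date, expenses, time and reasons, and nothing tells the patient whether fitting sensors or sending a wound picture is medical care. The Randomization and blinding section says patients are not blinded. The question arises mainly for experimental patients, so recorded time would depend on personal interpretation, chiefly in one arm.

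**Illustration of r (all inputs assumed except the 12 weeks).**

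r = minutes per day × days per week × 12 / 60

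| Minutes per day | Days per week | r, hours per experimental patient |
|---|---|---|
| 2 | 3 | 2 × 3 × 12 / 60 = 1.2 |
| 5 | 7 | 5 × 7 × 12 / 60 = 7.0 |
| 10 | 7 | 10 × 7 × 12 / 60 = 14.0 |

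As visit equivalents, r / v with v assumed to be 2 to 4 hours:

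- Lowest: 1.2 / 4 = 0.3 visits
- Middle case: 7 / 4 = 1.75 to 7 / 2 = 3.5 visits
- Highest: 14 / 2 = 7 visits

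The range runs from negligible to large. The middle case has no better support in the documents than either end.

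**The case against.** The strongest reply is that the text does not exclude remote care. The outcome's name covers medical care generally, the component list is introduced as what the outcome includes rather than as a complete list, and no sentence confines the diary to clinic visits. A reader might infer that the diary captures visits only and that app time scores zero. The documents do not say that; they leave the matter open.

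A reader might also infer that the gap always favours the device. That does not follow. Travel appears among the costs but not among the times, so a strict reading also drops the journeys that avoided visits would have saved. Control patients' calls to the team would go uncounted as well.

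The list of extra tasks should not be inflated either. Doctors help with downloading the app and connecting the devices, and this may happen before discharge. Uploading is optional, with no stated frequency. The videos have a counterpart in the control handbook. Sensor fitting is tied to exercising and could fairly be classed as exercise time.

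Finally, this is a condensed article, and diary instructions may sit in a fuller document. Visit time is also a legitimate outcome for a device meant to spare patients return visits.

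These replies limit the point but do not remove it. The article does more than leave a detail out: it states the time component of a primary outcome, and states it more narrowly than the outcome's name and the hypothesis. The generous reading leaves the classification to unblinded patients.

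**Conclusion.** The concern holds as a defect of definition. The time outcome names visit time alone and does not say whether remote-care time counts, although such care through the app and devices is provided to one arm only. Under the visit-only reading, a shift from clinic to app registers as time saved with no offset. Under the broad reading, what is recorded depends on unblinded patients' own judgement, mainly in the experimental arm. Neither supports an unqualified claim of time savings.

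Neither the net direction nor the size can be derived from the documents. The figures of 1.2 to 14 hours, or 0.3 to 7 visits, rest wholly on assumed handling time, frequency and visit length. They show only that the omitted time could matter. The point should be settled before recruitment because it decides what a positive result on this outcome would mean.

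**What to change.** Before recruitment, define the components of the time outcome and apply the same rule in both arms:

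- Add one diary entry type for remote-care time: uploads, messages or calls with the team, and device handling outside the exercise session. Control patients' calls count in the same way.
- State whether travel time counts.
- Report visit time and total time, and say which is the primary outcome.

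If visit time alone remains primary, word the hypothesis and the conclusion as clinic visit time rather than time savings.

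The cost is one entry type in a diary that patients already keep and a few sentences in the outcome definition. The downsides are slightly more diary burden and a possibly smaller observed saving. The Trial status section says the trial has not yet begun, so at that stage the change affects no collected data.

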### Randomization and blinding

The 200 recruited patients are randomly assigned in a 1:1 ratio to either the experimental or control group using a computerized random number generator. Each patient is assigned a random number. Blinding is not possible due to the nature of the study, so neither patients nor physicians will be blinded to their group assignment. However, data analysts will not have access to any patient information other than their assigned number and will remain blinded during the statistical analysis of the collected data and presentation of results.

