### Data analysis

The study schedule is depicted in Table 1. Data of all patients are recorded in Excel format and imported into SPSS (version 26.0; Armonk, New York, USA) for statistical analysis. To minimize bias due to missing data, intention-to-treat analyses and multiple imputation methods are employed. Descriptive statistics of measurement data are presented as mean ± standard deviation, while counting data are expressed as rate and composition ratio. Continuous variables are subjected to Student's *T* test if they meet the normal distribution, and Wilcoxon rank sum test is used otherwise. Categorical variables are tested using the chi-square test or Fisher's exact test. Secondary analyses are adjusted for baseline characteristics using analysis of covariance (ANCOVA). This study involves conducting multiple hypothesis tests, which undoubtedly increases the probability of Type I errors significantly. To control for family-wise error, Bonferroni corrections are adopted, resulting in a lowered adjusted *p* value of 0.002.

**Table 1 Tab1:** The patients’ schedule of trial enrollment, interventions, and assessment

Time point	Study period					
	Inpatient			Outpatient		
	Enrollment	Allocation	Pre-operation	2w	12w	24w
Enrollment						
Eligibility screen	×					
Informed consent	×					
Allocation		×				
Rehabilitation education			×			
Interventions						
Experimental group			×			
Control group			×			
Assessments						
Basal demographics and clinical data			×			
Cost					×	
Time					×	
6MWT						
ROM						
VAS						
KSS						
WOMAC						

“×” indicates the execution of the project according to the schedule

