### Limitations

Firstly, all participants were recruited from a single hospital located in the northwest region of China, which may limit generalizability to other populations. Secondly, there is a potential for response bias in this study, as the experimental group patients may alter their behavior when they are aware of being observed, showing greater compliance and less carelessness, and being more inclined to perform well. This potential for response bias may lead to exaggerate the differences in trial outcomes, and caution should be exercised when discussing the results.

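### Both primary outcomes rest on one unblinded patient diary with no described way to mark a period without cost, so gaps in a returned diary count as zero and escape the planned imputation

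*Protocol article*

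**What the plan says.** The Primary outcome section defines the two primary outcomes as "the cost and time spent on medical care within 12 weeks after discharge" and names one source for them: "All costs and time are recorded in a diary". It describes the content of the diary entry by entry: "Each entry in the diary must include the date, expenses, and time spent, along with the reasons". On who holds it: "The diary is provided to the patients in both groups by the physiotherapists before discharge for free".

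The Outcome measures section fixes when the totals are formed: "The cost and time are calculated at 12 weeks after discharge". Table 1 agrees, marking cost and time at 12 weeks only, although patients also attend at 2 weeks.

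Under Randomization and blinding, "neither patients nor physicians will be blinded to their group assignment"; only the data analysts are blinded. For missing data, the Data analysis section says that "intention-to-treat analyses and multiple imputation methods are employed". It does not say when a diary, or part of one, counts as missing.

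**The concern.** A diary described by its entries records what the patient wrote down. As described, a stretch without entries looks the same whether the patient spent nothing or stopped writing. When the entries are added up at 12 weeks, both cases contribute zero.

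This separates two kinds of incomplete data. A diary that never comes back gives no total, so it is visibly missing and imputation can act on it. A diary that comes back with gaps still gives a total. That total enters the analysis as an observed value that is too low, and nothing triggers imputation. Analysing patients in their randomised arm does not help either, because the error lies in the measurement.

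At stake are both primary outcomes. Similar under-recording in the two arms understates any real saving. Different under-recording adds a bias of either sign: poorer recording by control patients hides a saving, and poorer recording by experimental patients creates one. Blinding the analysts cannot repair entries made by patients who know their arm.

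**Working it through.** **Inputs from the Sample size section:** SD 3987 (unit not stated, taken as RMB), target difference 2000 RMB, two-sided α 0.05, power 0.90, 80 per group. From Data analysis: adjusted threshold 0.002.

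**Not in the document, so assumed:** the mean cost per arm and the share of cost that patients record.

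**1. The plan's own figure.** n = 2(1.960 + 1.282)² × 3987² / 2000² = 83.5, so 84 per group against the stated 80. That mismatch is a separate matter. Power at 80 is the baseline here:
- SE = 3987 × √(2/80) = 630.4 RMB
- 2000 / 630.4 = 3.173
- power at 0.05 = Φ(3.173 − 1.960) = 0.887
- power at 0.002 = Φ(3.173 − 3.090) = 0.53

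**2. Equal under-recording.** If both arms record a share r of true cost, the expected recorded difference is r × 2000. With the SD held at 3987:

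| Under-recording | Recorded difference (RMB) | Power at 0.05 |
|---|---|---|
| 0% | 2000 | 0.887 |
| 10% | 1800 | 0.815 |
| 20% | 1600 | 0.718 |
| 30% | 1400 | 0.603 |

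At 20% and the 0.002 threshold: 1600 / 630.4 = 2.538, and Φ(2.538 − 3.090) = 0.29.

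The constant SD matters. If every patient omitted exactly the same 20%, the SD would fall to 0.8 × 3987 = 3190 as well. The ratio 1600 / (0.8 × 630.4) would stay at 3.173, and so power at 0.887. The power loss therefore depends on omissions varying between patients, so that the spread does not shrink in step. The 20% understatement of the saving, 400 RMB, remains in either case.

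**3. Unequal recording, no true difference.** The false difference is the mean cost times the gap in the share recorded. Rejection rates at two-sided 0.05, with SE 630.4:

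| Assumed mean (RMB) | Gap of 5 points | 10 points | 20 points |
|---|---|---|---|
| 4000 | 200 RMB, 0.062 | 400 RMB, 0.097 | 800 RMB, 0.245 |
| 8000 | 400 RMB, 0.097 | 800 RMB, 0.245 | 1600 RMB, 0.718 |

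Worked cell: 4000 × 0.10 = 400; 400 / 630.4 = 0.635; Φ(0.635 − 1.960) + Φ(−0.635 − 1.960) = 0.097.

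These tables show sensitivity. They do not estimate what will happen in this trial.

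**The case against.** The strongest reply is that this is a condensed article. Diary layout, nil entries, receipt checks and a rule for partly filled diaries may stand in the full protocol or on the diary form. The article says what an entry must contain and does not forbid nil or periodic entries. A diary is also a defensible source for transport and time, which a hospital's charge records would not hold.

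Much of this stands, and it limits the point. It does not remove it, because the article makes a positive choice: one self-reported source for everything in both primary outcomes, totalled once, with imputation as the stated protection against missing data. If checks exist, a sentence saying so settles the matter.

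Several stronger readings go beyond the text:
- **Completeness will probably differ by arm.** A reader might infer this from the Limitations section, which expects observed patients to change, "showing greater compliance and less carelessness, and being more inclined to perform well". That section does not mention the diary, and both arms get the same diary from the same staff. It also expects differences to be exaggerated, whereas fuller recording in the experimental arm would raise that arm's recorded cost and hide a saving.
- **Experimental patients will log contacts in the APP instead.** The APP is described as receiving functional and symptomatic information, not visits or costs.
- **The hospital already holds the figures.** The article mentions no billing records and does not say that care after discharge is obtained there.
- **Imputation is useless here.** It can still act on diaries that are not returned.

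**Conclusion.** The point holds as a weakness in how the primary outcomes are measured. As described, a returned but partly filled diary yields a low total that the stated missing-data method would not recognise as incomplete. How often this will happen, and whether it will differ by arm, cannot be read from the document, so neither the size nor the direction of a bias is established.

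The illustration of 20% equal under-recording costs 400 RMB of a 2000 RMB difference. The accompanying power loss, 0.887 to 0.718 at 0.05 or about 0.53 to 0.29 at 0.002, assumes an unchanged SD and would be smaller if the spread shrank too. The stricter threshold leaves little room for measurement loss. The change should be made because it is cheap and lets the planned imputation do its work, not because a bias has been shown.

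**What to change.** In the Primary outcome section, for both arms alike:

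1. Add a weekly box to the diary stating *no medical cost or time this week*. Treat a week with neither an entry nor a tick as missing and impute it. State this rule alongside the multiple imputation in Data analysis.
2. Have staff go through the diary with the patient at the existing 2-week and 12-week visits, against receipts where available, using the same procedure in each arm.
3. Where the study hospital's charge records can be obtained, use them to cross-check entries for care given there, without counting any item twice. The cross-check should leave the definition of cost as it is.

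Cost: a changed diary page and a few minutes at two visits already planned. Trial status describes the trial as not yet begun, so this can be settled before the first diary is handed out.

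Remaining limits: time, transport and costs at outside providers stay self-reported, and a visit left out of a week that contains another entry will not be detected by the box.
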